## Methods

### Study design

In a cluster randomised trial, we will evaluate if a year-long behavioural intervention bundle in a rural setting in Burkina Faso (Nanoro district) and in the Democratic Republic of Congo (DRC) (Kimpese district) has a superior outcome on a range of standardised AMR and WaSH indicators in intervention and control villages. Controlled measurements of antibiotic use (patient surveys), patient management (mystery patients) and water-sanitation-hygiene (household surveys) will be collected in the same season before and after. In each setting, eligible villages and town neighbourhoods (clusters) will be randomly allocated to intervention or no intervention (control). Randomisation is in two strata per site. In Nanoro, strata distinguished villages with primary health centre and those without (only formal or informal medicine outlets). In Kimpese, strata distinguished peri-urban neighbourhoods of rural villages. For each stratum, clusters (villages or neighbourhoods) are randomised 1:1 as intervention or control. A random number between 0 and 1 is given to each cluster using the RAND() function in Excel by a local data manager not involved in the trial. Half of the cluster in each of both strata, those with the higher numbers, are selected as intervention clusters; the other half, with the lower numbers, as control clusters. Allocation of villages to intervention or control was concealed until all had been recruited and baseline data available.

By randomising communities rather than individuals, contamination of intervention and no intervention should be maximally avoided, as supported by pilot studies in the DRC that observed that >80% of social contacts were with people in the same village or neighbourhood (manuscript in preparation). A steering committee consisting of the PIs of all 7 participating institutes will meet at least annually to discuss progress, and at least annually full consortium meetings will be organised with options for on-line participation.

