### Sample size

The sample size is based on the primary outcome. Including in each setting 22 clusters, with per cluster 100 patients to be interviewed upon exiting a medicine store, a frequency of Watch antibiotic use of 24% in DRC [13], and assuming an estimated intraclass coefficient of 0.05, a cluster level correlation (rho_c_) of 0 (conservative), subject level correlation (rho_s_) of 0 (different subjects at baseline and at 12 months), our study has 80% power to observe a 40% reduction in Watch antibiotic use.

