
### Analysis

The effect evaluation will use standard experimental methods and will make use of multilevel statistical models (to account for clustering within villages and households), including time*intervention interactions. The population’s socio-demographics, socio-economic status, healthcare use and health behaviour are regularly recorded during scheduled HDSS rounds, which will allow subgroup analyses of the effect of the intervention.

Based on the exit interviews, the proportion of primary care or medicine outlet visits resulting in dispensing of Watch antibiotic courses will be estimated, adjusted for clustering, in the intervention and in the control groups before and 12 months after the start of the intervention. Antibiotics will be grouped as Access, Watch or Reserve (AWaRe) according to WHO’s 2019 AWaRe classification. Patients’ antibiotic treatment dose, dosage, duration, mode of administration and uptake will be assessed, to determine the Defined Daily Doses (DDD) each treatment course accounts for. We assess for each treatment course whether the treatment is underdosed, based on the 2022 WHO AWaRe Antibiotic Book. A case management score is deducted using the scoring grid to be completed after each simulated patient visit. The change in frequency of Watch antibiotic use and in mean case management score before and after the intervention (months 0 and 12) will be compared to that during the same period in the control areas. We will determine risk differences and risk ratios, which will be adjusted for socio-economic indicators and other potential confounding factors. Linear and non-linear regression models will be used to estimate the effect and carry out subgroup analyses.

Stool samples will be cultured on selective CHROMagar™ plates and species identified. If *E. coli* and/or *Salmonella* isolates are detected, they will be typed and antibiotic susceptibility testing done according to CLSI guidelines for pathogen-antibiotic indicators and for ESBL, if the minimal inhibitory concentration for ceftriaxone or ceftazidime is above 1 mg/L.

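### Comparing before-after change between arms gives away precision that adjusting for each cluster's baseline would keep: variance ratio 0.50 at the plan's rho_c of 0, 0.84 at rho_c of 0.8

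*Protocol article*

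**What the plan says.** The Analysis section defines the comparison in two steps: "The change in frequency of Watch antibiotic use and in mean case management score before and after the intervention" is measured at months 0 and 12, and it "will be compared to that during the same period in the control areas". The estimation tool is "multilevel statistical models (to account for clustering within villages and households), including time*intervention interactions". Risk differences and risk ratios are promised, "adjusted for socio-economic indicators and other potential confounding factors". The baseline value of the outcome is not named among the adjusters.

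The Sample size section plans on "Including in each setting 22 clusters, with per cluster 100 patients to be interviewed upon exiting a medicine store", an intraclass coefficient of 0.05, "a cluster level correlation (rho_c_) of 0 (conservative" by its own label, and a subject-level correlation of 0 because the patients differ between rounds.

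On design, the Study design section states: "For each stratum, clusters (villages or neighbourhoods) are randomised 1:1 as intervention or control". It adds: "Allocation of villages to intervention or control was concealed until all had been recruited and baseline data available".

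**The concern.** A difference of changes fixes the coefficient on the baseline at 1, however weakly the baseline predicts follow-up. When the same clusters are surveyed twice with different patients, the right coefficient is the correlation r between a cluster's two survey means (with equal variances), and that is below 1. Subtracting the whole baseline then adds noise. If r is below one half, the change contrast is less precise than ignoring the baseline altogether.

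The usual reason to accept this cost is protection against systematic baseline differences. It does not apply here, because clusters are randomised and the baseline was collected before allocation was disclosed. With 11 clusters per arm in each country and the cluster count already fixed, the analysis is one of the few places where precision can still be gained.

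**Working it through.** **Inputs.** From the Sample size section: 22 clusters per country, m = 100 patients per cluster (read as per survey round), control proportion 0.24, a 40% reduction (to 0.144), ICC 0.05, rho_c = 0, rho_s = 0. From Study design and the Abstract: 1:1 allocation, so 11 clusters per arm. Alpha is not stated; two-sided 0.05 is assumed.

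**Correlation of a cluster's two survey means.** Design effect DE = 1 + 99 × 0.05 = 5.95. With rho_s = 0, r = [m × ICC / DE] × rho_c = (5/5.95) × rho_c = 0.84 × rho_c.

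**The plan's own figure.** Variance of a follow-up-only comparison with 11 per arm: (0.24 × 0.76 + 0.144 × 0.856) × 5.95 / 1,100, giving SE 0.0407. Power = Φ(0.096/0.0407 − 1.96) = 66% (65% with pooled variance, 61% with a t reference). The stated 80% is not reproduced. At rho_c = 0 the adjusted analysis has the same 66% in large samples, and the change contrast has 36–39%.

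**Variance factors relative to follow-up only.** Change contrast: 2(1 − r). Baseline-adjusted: 1 − r². Ratio adjusted/change: (1 − r²)/[2(1 − r)] = (1 + r)/2.

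| rho_c | r | change, 2(1−r) | adjusted, 1−r² | ratio | power, change | power, adjusted |
|---|---|---|---|---|---|---|
| 0 | 0 | 2.00 | 1.00 | 0.50 | 36–39% | 66% |
| 0.5 | 0.42 | 1.16 | 0.823 | 0.71 | 55–59% | 74% |
| 0.8 | 0.672 | 0.655 | 0.548 | 0.84 | 79–83% | 89% |
| 1 | 0.84 | 0.319 | 0.294 | 0.92 | 97–99% | 99% |

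The upper power for change multiplies the follow-up-only variance by 2(1 − r). The lower one gives both arms the 24% binomial variance at baseline, which is what randomisation implies.

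**Finite-sample check.** 20,000 simulated trials per value of rho_c, 11 against 11 clusters, cluster-level analyses with t tests:

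| rho_c | ratio, no effect | ratio, planned effect | power, change | power, adjusted |
|---|---|---|---|---|
| 0 | 0.52 | 0.49 | 33% | 60% |
| 0.5 | 0.75 | 0.68 | 52% | 68% |
| 0.8 | 0.88 | 0.78 | 75% | 84% |
| 1 | 0.97 | 0.87 | 96% | 98% |

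Type I error was about 5% for both analyses throughout.

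**Cost of estimating the slope.** With 22 clusters, variance rises by about 1 + 1/18 = 1.056. Adjustment stays ahead while 1.056 × (1 + r)/2 < 1, that is r < 0.89. Under the plan's ICC and cluster size, r cannot exceed 0.84.

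**Does the multilevel model avoid the loss?** Not as worded. With a free arm difference at baseline and balanced data, the interaction term is the difference of changes. The precision returns only if the arms share a baseline mean or the cluster baseline is a covariate.

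**The case against.** The strongest reply is that the article does not fully fix the estimator. It does not say whether an arm term at baseline is fitted, and a common-baseline model is itself a time-by-arm model with that term left out. That reading is possible. But the text sets change against change and lists its adjusters without the baseline outcome, so the natural reading is the unconstrained contrast.

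The second reply is that rho_c = 0 is a floor and not a forecast. This stands. Surveys are repeated in the same clusters at the same season, so some positive correlation is plausible, although the document gives no value. The gain must therefore be shown over a range.

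Four stronger readings are tempting and not supported:

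- A reader might infer that the planned analysis is biased. It is not: randomisation and concealment make both contrasts unbiased.
- A reader might infer that adjustment always wins. That is a large-sample result. At an assumed ICC of 0.10, r could reach 10/10.9 = 0.92, above the 0.89 break-even for 22 clusters.
- A reader might infer that the variance is halved whatever happens. That holds only at rho_c = 0.
- A reader might infer that this is the largest recoverable share of power. Pooling the two countries raises power for change from 55% to 84% at rho_c = 0.5 and from 79% to 97% at 0.8; adjustment within a country reaches 74% and 89%. Pooling recovers more at both values.

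**Conclusion.** The point holds as a matter of efficiency. The planned contrast is valid, but under the stated ICC and cluster size it is less precise than a baseline-adjusted estimate from the same data. The variance saving is 50% at rho_c = 0, 29% at 0.5 and 16% at 0.8, and little remains near 1. The power gain per country is about 27–30, 15–19 and 6–10 points at those first three values, and small-sample methods put power a few points lower for most of these entries.

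The power figures rest on an assumed two-sided alpha of 0.05, 100 patients per cluster per round, ICC 0.05 and no correlation between patients across rounds. The formula (1+r)/2 applies equally to the case management score, but the document gives no ICC or visit count for it, so no size can be stated there. The failure to reproduce 80% power is a separate matter: at rho_c = 0 neither analysis reaches it with 11 clusters per arm.

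**What to change.** Make the primary estimate the arm difference at month 12 adjusted for the cluster's baseline Watch proportion. Alternatively, use a mixed model with a common baseline mean, a period effect, an arm-at-follow-up effect, and village and village-by-period random effects. Cluster-level adjustment of proportions gives a risk difference but no direct risk ratio. If both promised measures are to come from one analysis, use the mixed model and derive both from it. Treat the case management score in the same way, and keep the unconstrained interaction as a sensitivity analysis. State alpha, and show power over a range of rho_c.

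The change uses data already in the plan and adds no fieldwork. It should be written down before follow-up data are analysed. If it is handled as a protocol amendment, the Ethical approval section requires ethics approval and an update of the registry entry, so there is a modest administrative cost.

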### Data management

A full data management plan has been drafted for the project in line with the requirements of the funders, and agreed upon by all partners, detailing all important aspects with regard to data management, data protection and open access to data. European researchers subscribe to the European Code of Conduct for Research Integrity. These policies ensure data integrity, traceability and confidentiality. Project data will be shared between consortium members on a need-to-know basis. Since personal data is collected and processed, the project will comply with the EU General Data Protection Regulation (GDPR 2016/679). Anonymisation or at least pseudonymisation will be done at the earliest opportunity and as much as possible. No participant-identifiable data will be disclosed from study intervention sites/partners, nor in study databases, analysis and reports. User roles and access controls for study-sensitive data will be implemented. Controlled access to confidential data can be granted on a need-to-know basis, involving a local data access committee. Data storage will be done on centrally secured and protected servers or clouds, with secure (encrypted) transfers of study confidential data if needed. Data retention periods will be in line with legal and data protection requirements but will be at least 5 years after completion of the research.

### Dissemination

Results will be shared with the local HDSS and health authorities in interactive meetings and with posters. National and international authorities will be informed with policies briefs. Press releases will encourage the regular media to include information for the general public in their publications. Scientific results will be disseminated via peer-reviewed and (in principle) open-access publications in non-predatory journals, and through presentations in AMR networks. Pseudonymised data will be open access on a study repository, following the publication of results.

### Ethical approval

Ethical approval for the final protocol vs 1 has been obtained from the Institutional Review Board of the Institute of Tropical Medicine, Antwerp, Belgium (1559/22, dd 29032022; 1566/22, dd 24052022), from the Ethics Committee of the Antwerp University Hospital, Belgium (3363, dd09052022; 3456, dd 24052022), from the Ethics Committee for Health Research in Burkina Faso (2022-03-050, dd 02032022), and from the Ethics Committee of the Université Protestante au Congo, DRC (CEUPC0098, dd 31032022).

Informed consent for the intervention is collected orally from village chiefs and documented, and written consent if obtained from participating health care providers or medicine dispensers. For patients’ participation to the exit surveys and for household heads’ participation to the household surveys, written informed consent is obtained.

A risk management plan has been included in the proposal.

In case of protocol amendments, following ethical approval, funders will be informed, and the revised protocol will be updated in the clinical trial registry. Any deviations from the protocol will be fully documented using a breach report form.

A data Monitoring Committee was not considered indicated as this behavioural intervention with no individual interventions or follow-up, and with data collection only at baseline data before the start of the trial and upon completion of the trial. Interim analysis or stopping rules therefore also do not apply.

## Discussion

To combat the complex drivers of AMR, in line with recommendations from WHO and the World Organisation of Animal Health (OIA), a context-specific approach is needed which both promotes rational use of antibiotics, and optimal prevention of transmission. Our project proposes a robust participatory-driven behaviour change intervention to reduce the need and use of (Watch) antibiotics from formal and informal medicine stores, targeting both the demand (community) and supply (medicine store) side, to improve the quality of care of frequent clinical presentations from infectious disease, and to reduce emergence and transmission of AMR. A process evaluation after the second and third rounds of the intervention is therefore planned in a number of intervention villages in each country to better understand the contribution of each element of the intervention to intervention impact, as well as the processes underlying intervention impact.

The epidemiological before-after evaluation in intervention and control villages as described will assess the impact of this year-long intervention on actual antibiotic use, self-reported WaSH and health literacy changes, and clinical care by the medicine stores. The projected long-term impact of the intervention bundle on AMR transmission will be estimated via mathematical modelling, combining these outcomes with estimates of within-household AMR pathogen or gene transmission rates, estimates of AMR prevalence, and estimated environmental exposure. We will fit Markov models to longitudinal household data derived from repeated stool samples which will enable estimation of the rate of person-to-person transmission within households, the rate of loss of detectable carriage within individuals, and the association of these rates with the study intervention and baseline household covariates.

At the same time, it will be key to develop sustainable One Health surveillance to keep track of AMR changes over time and place, as these might signal the need for modification of control activities. In a sub-study in DRC, we will already pilot environmental surveillance with rodents (as sewage surveillance is not an option) in parallel to the community sampling, and we are planning to evaluate the possibilities of pooled metagenomic One Health surveillance of different clinical sources and potential environmental reservoirs, to monitor trends and predict clinical susceptibilities and AMR.

### Limitations

There are a number of limitations to this study. If proven effective, it is quite human resource intensive, as most complex interventions, which could raise some concerns about sustainability and scalability. Nevertheless, the cost of unrestricted further increases in AMR will far outweigh those of preventive interventions. Furthermore, we are convinced that the only sustainable way to change behaviour is by a joint, bottom-up process to have a common understanding with all stakeholders of problems and solutions. For sustained impact, it is likely indicated to have regular refresher meetings to maintain motivation, in view of many other daily life challenges faced by people in low-resource settings. By involving policy makers from the start, we hope to ensure they will be motivated to organise their preventive services in such a way as to enable this. However, there is always the risk that the prevention paradox means that policy makers are less inclined to invest in problems that are not directly visible. Follow-up studies should therefore address the cost-effectiveness of community-based interventions, and at the same time explore to what extent they could be supported by other community-driven activities, e.g. strengthened One Health surveillance at the community level, which is possible with the pooling of samples.

Furthermore, although we intended to demonstrate the added value of this innovative approach, we realise that the developed intervention itself is not generalisable nor reproducible as such by design. It requires co-creation and context-specificity to achieve the buy-in of participants and the appropriateness of the intervention elements aimed to nudge towards appropriate use of antibiotics and improved infection control practices.

Additionally, patient exit surveys are the most suited method to measure the prevalence and quantify of antibiotic use during visits to medicine stores across different provider types, yet an assessment of the appropriateness of antibiotic use is impossible in the absence of a detailed clinical assessment with extensive diagnostic tools. Moreover, antibiotic dispensing might be different -more desirable - among patients visiting the provider at the time an interviewer is present. Similarly, answers to household surveys might reflect what is considered more desirable, compared to day-to-day behaviour. We addressed this by adding to the questionnaire as much as possible observations by the interviewer. We will assess the risk of bias by comparing changes in reported behaviour to observed behaviour change. Finally, simulated patient visits are limited by the number of clinical presentations they can assess, in turn, limited to presentations that would not require invasive procedures and that are acceptable and feasible.

### Trial status

Following external peer review, the study protocol was selected by JPI for funding on 28 October 2021 (JPIAMR2021-053) with a total budget of 1.6 million Euro, and registered at www.clinicaltrials,gov on 13 May 2022 (NCT05378880). In 2022, the development of the intervention bundles and materials took place through a co-creation process with the communities, per country 22 clusters were identified, and pre-trial data collection started in both arms. Implementation of intervention bundles started in February 2023 and is ongoing, with post-intervention bundle data collection in both intervention and control villages expected to be completed by summer 2024 (Figs. 3 and 4).

**Fig. 3 Fig3:**
[figure not shown]
Workplan

**Fig. 4 Fig4:**
[figure not shown]
Spirit-figure CABU-EICO with schedule of enrolment, interventions, and assessments. See also Fig. 3 for details

## Abbreviations

AMR: Antimicrobial resistance
AWaRe: Access-Watch-Reserve antibiotics (WHO classification)
BF: Burkina Faso
DDD: Defined daily dosis
DRC: Democratic Republic of Congo
ESBL: Extended spectrum beta lactamase
HDSS: Health Demographic Surveillance Site
JPI: Joint Programme Initiative
LMIC: Low and middle-income country
OIA: Organisation Animal Health
sSA: Sub-Saharan Africa
WaSH: Water, Sanitation, Hygiene
WHO: World Health Organisation
